**Fig. 1 Fig1:**
[figure not shown]
Flow chart of subjects through the MARKO study

**Table 2 Tab2:** List of subjects’ assessment through different stages of MARKO study

Assessment	Time/place						
	0	2-4	6	12	18	24	60
		w	m	m	m	m	m
	GP	P	GP	GP	GP	P	P
Prescreening	X						
Informed consent	X						
Inclusion/exclusion criteria	X						
MARKO questionnaire	X	X				X	X
CAT		X				X	X
SGRQ		X				X	X
History		X				X	X
Physical		X				X	X
EBT before and after cigarette		X					
Lung function							
COPD-6™	X	X	X	X	X		
Spirometry with bronchodilator test		X				X	X
Impulse oscilometry^a^		X					
Lung diffusion capacity		X					
Body plethysmography^a^		X					
Blood sampling (hematology; highly sensitive C-reactive protein; blood							
stored for DNA, RNA, plasma and serum)^b^		X					
Functional exercise capacity (6-minute walk test)		X					
COPD diagnosis		X				X	X

Legend: w - week, m - month, GP - general practitioner’s office, P - pulmonologist at tertiary care hospital, CAT - COPD Assessment Test, SGRQ - St. George Respiratory Questionnaire, EBT - exhaled breath temperature

^a^Impulse oscilometry and body plethysmography was done only in one center

^b^Blood sampling was done only in subjects that signed additional Informed consent

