
In Phase II up to 500 subjects will be recruited from Phase I, assessed by designated pulmonologists as ‘healthy’ smokers, symptomatic smokers (GOLD 0) and as COPD GOLD 1. Selected subjects will be followed for at least 5 years; first assessment after 2 years (±2 months) and the second 5 years (±2 months) after the baseline. During the first 2 years of follow-up all subjects will have regular lung function measurement using COPD-6^TM^ at their GP’s office in 6 month intervals. All subjects will be assessed by the same pulmonologist for diagnosis and severity of COPD according to GOLD and ATS/ERS after 2 and 5 years for the progression of disease defined by three outcome measures: (1) newly diagnosed COPD (ND COPD); (2) disease progression (DP; newly diagnosed COPD + progression to higher severity stage); and (3) high rate of loss of lung function (LoLF; >70 mL/year for post bronchodilator FEV_1_). Incidence of newly diagnosed COPD after 2- and 5-years of follow up will be used to identify diagnostic parameters that are most sensitive for early impairment in COPD, to determine the predictability of developed screening MARKO questionnaire alone or with other markers of early impairment in COPD. Blood samples from a subsample of patients who give the consent for omics research will be used to develop omics markers predictive for the future development of COPD and disease progression.

This research will attempt to answer to following questions: (1) can we identify cheap and simple tools that will allow a precise and accurate identification of subjects from a population at risk of developing COPD in the future; (2) is there a combination (pattern) of tools, functional parameters, genetic and biochemical markers that can reliably predict the development of COPD in a population at risk, thus allowing early intervention.

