### Lung function

Spirometry was performed using computerized pneumotachographs (Jaeger®, CareFusion, CA, USA) using the same procedure at all clinical sites (lung function labs at tertiary hospitals) in agreement with the ATS/ERS standardization [15]. The best of three technically satisfactory efforts was recorded. Bronchodilator test was done with repeated spirometry 20 min after inhalation of 400 mcg of salbutamol using the inhalation chamber. Spirometric parameters (FVC, FEV_1_, FEV_1_/FVC ratio, peak expiratory flow [PEF], forced expiratory flow between 25 and 75% FVC [FEF_25–75_]) were recorded as absolute values and as percentage of predicted according to Quanjer [16].

Impulse oscillometry (IOS) was done using Jaeger MasterScreen IOS (Viasys Healthcare, Inc., Yorba Linda, USA) for measurements of respiratory system impedance according to ATS/ERS recommendations and the following IOS data were collected: resistance of the respiratory system at 5 Hz (R_5_) and 20 Hz (R_20_) and reactance at 5 Hz (X_5_) [17]. Results were analyzed as absolute values and as percentages of predicted values (%) according to reference equations provided by the manufacturer [18].

Lung volume studies were carried out using a body-plethysmograph (Ganzhorn, Germany) according to ATS/ERS recommendations [19]. The following parameters were analyzed: airway resistance (RAW), expiratory airway resistance (RAWex), total lung capacity (TLC), residual volume (RV) and the RV/TLC ratio and expressed as percentages of predicted values according to ATS/ERS recommendations [19, 20].

Single-breath diffusing capacity of the lung for carbon monoxide (DL_CO_) was measured using a rapid carbon monoxide and helium analyzer (Ganzhorn, Germany), which was calibrated prior to each measurement. Values for DL_CO_ and DL_CO_ corrected for alveolar volume (V_A_) [DL_CO_/V_A_] were obtained and are reported as percent predicted values [21].

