Phase II data analysis will focus on secondary validation of the MARKO questionnaire to determine the construct validity and predictability (alone or in combination with other markers) for future development and/or progression of COPD. Construct validity of the MARKO questionnaire will be assessed using factorial analysis to confirm the number of factors the questionnaire is measuring with calculations of inter- and intracorrelations between the factors and items. Primary objective will be to create a questionnaire with the smallest number of items with reliable predictive properties. Identifying items for potential deletion will be based on a hierarchical process: age and sex bias, floor and ceiling effects, item to total correlation and tests of redundancy (inter-item correlation). Rasch analysis will be used to identify items with the best fit to a predictive model. Utility of different markers for disease progression will be assessed using generalized linear/nonlinear regression models and expressed as odds ratio (OR) with 95% confidence intervals (CIs). Predictive power for the models will be presented using receiver operator curve (ROC) analysis with AUC (with 95% CIs) together with associated criterion, sensitivity, specificity and positive (PPV) and negative predictive (NPV) values. *P* < 0.05 will be used as statistically significant for all analyses with correction for multiple comparisons.

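### The 2-year LoLF label rests on two FEV1 sessions and a 140 mL cut-off with no allowance for measurement error; analyse the continuous slope and treat 2-year LoLF as exploratory

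*Protocol article*

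**What the plan says.** The Phase II paragraph of the protocol article (Methods, aim, design and setting) has every subject assessed "after 2 and 5 years for the progression of disease defined by three outcome measures". The third measure is "high rate of loss of lung function (LoLF; >70 mL/year for post bronchodilator" FEV1). The timing is "first assessment after 2 years (±2 months) and the second 5 years (±2 months) after the baseline".

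In Table 2 the row "Spirometry with bronchodilator test" is marked at 2-4 weeks (the hospital baseline), 24 months and 60 months, and nowhere else. Between hospital visits, "all subjects will have regular lung function measurement using COPD-6" at the GP's office. That is a different device, and no bronchodilator is mentioned for it. Within a session, "The best of three technically satisfactory efforts was recorded" (Lung function section).

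Under Data analyses, the Phase II paragraph states: "Utility of different markers for disease progression will be assessed using generalized linear/nonlinear regression models and expressed as odds ratio", with ROC curves and AUC for the models. A separate sentence in the Phase II paragraph of the Methods gives the outcome for choosing markers: "Incidence of newly diagnosed COPD after 2- and 5-years of follow up will be used to identify diagnostic parameters".

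The article does not say how the annual rate is computed. It also gives no between-visit FEV1 variability, slope distribution or expected LoLF prevalence.

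**The concern.** A yearly rate taken from two sessions two years apart carries the full error of both sessions, divided by only two years. Taking the best of three efforts controls error within a session, not between sessions. If the between-session error is comparable with 140 mL, many subjects cross the threshold through noise, and some true fast decliners fail to cross it.

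Two results would suffer. The reported share of fast decliners at 2 years would be too high. Odds ratios and AUCs against the label would also be distorted, and not equally for all candidates. Markers unrelated to FEV1 error are pulled toward no association. Baseline lung function, also a named candidate, shares the baseline reading with the outcome and can gain an association it does not have. The noise would then favour lung function over the questionnaire that the study exists to validate.

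**Working it through.** The plan gives no figure for LoLF to reproduce; its one power statement concerns questionnaire scores.

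**Inputs from the article:** threshold 70 mL/year; hospital spirometry at 0, 2 and 5 years; follow-up windows of ±2 months.

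**Assumed, because the article gives none:** session SD s = 60-150 mL; true decline with mean 35-50 and between-subject SD 25-50 mL/year; normal distributions; independent session errors of equal SD; a marker correlated 0.5 with the true slope. The central case is mean 40, SD 30, s = 100.

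**1. Cut-off.** 70 × 2 = 140 mL. Across the window it is 70 × 22/12 = 128 to 70 × 26/12 = 152 mL. At 5 years it is 70 × 5 = 350 mL.

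**2. Slope error, for any s.**
- Two readings: √2 × s / 2 = 0.707 s.
- Three readings at 0, 2 and 5 years: the mean time is 7/3, and the sum of squares is (7/3)² + (1/3)² + (8/3)² = 12.67, so the error is s/√12.67 = 0.281 s.
- Ratio: 0.707/0.281 = 2.5.

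**3. Noise against the cut-off.** The SD of a two-session difference is √2 × s: 85, 141 and 212 mL for s = 60, 100 and 150. It equals 140 mL only if s is about 99 mL.

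**4. Central case.**
- True LoLF: P(slope > 70) = 1 − Φ(30/30) = 16%.
- At 2 years: error SD 70.7; observed slope SD √(900 + 5,000) = 76.8; labelled 1 − Φ(30/76.8) = 35%; reliability 900/5,900 = 0.15.
- With three readings: error SD 28.1; observed slope SD √(900 + 789) = 41.1; labelled 1 − Φ(30/41.1) = 23%; reliability 0.53.
- The true share among labelled subjects is P(true and observed > 70)/P(observed > 70), with correlation √reliability between the two slopes: 27% at 2 years, 47% with three readings.
- The marker's correlation falls to 0.5 × √reliability, so its AUC goes from 0.76 to 0.59 at 2 years and to 0.68 with three readings.

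**5. Range, by the same formulas.**

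| Mean / slope SD / s | True LoLF | Labelled at 2 y | Labelled who are true | AUC: true → 2 y → three readings |
|---|---|---|---|---|
| 35 / 25 / 150 | 8% | 37% | 12% | 0.78 → 0.55 → 0.62 |
| 40 / 30 / 100 | 16% | 35% | 27% | 0.76 → 0.59 → 0.68 |
| 50 / 50 / 100 | 35% | 41% | 56% | 0.73 → 0.63 → 0.70 |
| 50 / 50 / 60 | 35% | 38% | 67% | 0.73 → 0.68 → 0.72 |

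The session SD above which fewer than half the labels are true is 36 mL at mean 40, SD 30; 93 mL at 50, 40; and 144 mL at 50, 50.

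**6. Markers sharing the baseline reading.** These were simulated with no true association, at assumed SDs of 700 mL for FEV1 and 80 mL for true bronchodilator response, and with half the error variance at day level. Baseline post-bronchodilator FEV1 then shows an AUC of 0.52-0.57 for 2-year LoLF, and bronchodilator response 0.56-0.64. The baseline reading has weight 1/2 = 0.50 per year in the two-reading slope and (7/3)/12.67 = 0.18 in the three-reading slope, so the coupling weakens but does not vanish.

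**7. Cost of the cut itself.** In the central case at 2 years, the cut lies 30/76.8 = 0.39 SD above the mean. The information kept is φ(0.39)²/(0.35 × 0.65) = 0.137/0.227 = 0.60, so the continuous slope carries about 1/0.60 ≈ 1.7 times as much.

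**The case against.** Several objections have force.

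- **Noise is assumed.** A reader might infer that most subjects labelled at 2 years are not fast decliners. The article does not support that as a fact: modest changes in the assumptions put the true share above half (53% at mean 50, SD 40, s = 80; 67% in the last table row). This stands, so only a range can be given.
- **Not every marker is pulled toward null.** A reader might infer a uniform attenuation. Step 6 shows otherwise for baseline lung function. This also stands.
- **A good marker would still be seen.** An AUC of 0.59 with 500 subjects, 35% labelled, has a standard error of about 0.027, so it lies about 3.3 standard errors above 0.5. Performance is understated, not hidden.
- **LoLF is not the named selection outcome.** Newly diagnosed COPD is, and the primary endpoint also concerns developing COPD. LoLF is the third of three measures, and a 5-year assessment is already planned. This limits the reach. It does not remove the point, because the Data analyses section assesses markers for disease progression, and LoLF is one of the measures that define it.
- **The rate calculation may be in a fuller plan.** That is fair for the formula. But the threshold, the visits and the 2-year reading are fixed in the article, and no formula takes the error out of two readings. The stated regression models do not exclude a slope analysis, so the change proposed is compatible with the plan.

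**Conclusion.** The point holds in a limited form. From the article alone, assuming only independent session errors of equal size, a 2-year LoLF label is a 140 mL difference between two sessions, and its slope is 2.5 times as noisy as the three-reading slope.

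The consequences depend on the assumed ranges. At 2 years the labelled share is about 1.1 to 4.6 times the true share (38/35 to 37/8 in the table, before rounding). Attenuation for markers with independent error occurs even in the most favourable case (AUC 0.73 to 0.68). The direction can reverse for markers built on the baseline spirometry.

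The documents do not support saying that the study's marker selection fails, since that is tied to newly diagnosed COPD. The 5-year LoLF is better but not clean: 47% of labels are true in the central case. This is a worthwhile, inexpensive improvement to a secondary progression measure.

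**What to change.** In the Phase II paragraph of the Methods and the Phase II paragraph of Data analyses:

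- Analyse loss of lung function as the continuous post-bronchodilator FEV1 slope (mL/year), in a linear mixed model with a marker-by-time term, over all hospital readings (baseline, 24 and 60 months) at their actual dates.
- Report the proportion above 70 mL/year as a secondary summary, from the 5-year slope.
- Label any 2-year LoLF result exploratory. Where the marker is itself a baseline lung-function measure, state that it shares a reading with the outcome; the mixed model does not remove that link.
- Do not add the GP COPD-6 readings to this model. No bronchodilator is stated for them, a device offset cannot remove subject-specific bronchodilator response, and Table 2 has no COPD-6 reading at 24 months.

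The cost is analysis wording and one model on data already scheduled, with no new visit or measurement. The downside is that a firm LoLF result waits for the 5-year visit.

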### Other HRQoL questionnaires

HRQoL will be additionally assessed using 2 standard questionnaires; St. George Respiratory Questionnaire (SGRQ) and COPD Assessment Test (CAT). The SGRQ is a standardized self-administered airways disease-specific questionnaire divided into three subscales: symptoms (8 items), activity (16 items), and impacts (26 items). SGRQ scores were calculated using score calculation algorithms and missing data imputation (if the total number of missing items was ≤10) using the Excel® SGRQ calculator. For each subscale and for the overall questionnaire, scores range from zero (no impairment) to 100 (maximum impairment) [10, 11]. The CAT is a validated, short (8-item) and simple patient completed questionnaire, with good discriminant properties, developed for use in routine clinical practice to measure the health status of patients with COPD. Every item has a scale of 0–5 so the scoring range is from zero (no impairment) to 40 (maximum impairment) [13]. Both HRQoL questionnaires were self-completed by patients before any other procedure was done and after the MARKO questionnaire.

### Lung function

Spirometry was performed using computerized pneumotachographs (Jaeger®, CareFusion, CA, USA) using the same procedure at all clinical sites (lung function labs at tertiary hospitals) in agreement with the ATS/ERS standardization [15]. The best of three technically satisfactory efforts was recorded. Bronchodilator test was done with repeated spirometry 20 min after inhalation of 400 mcg of salbutamol using the inhalation chamber. Spirometric parameters (FVC, FEV_1_, FEV_1_/FVC ratio, peak expiratory flow [PEF], forced expiratory flow between 25 and 75% FVC [FEF_25–75_]) were recorded as absolute values and as percentage of predicted according to Quanjer [16].

Impulse oscillometry (IOS) was done using Jaeger MasterScreen IOS (Viasys Healthcare, Inc., Yorba Linda, USA) for measurements of respiratory system impedance according to ATS/ERS recommendations and the following IOS data were collected: resistance of the respiratory system at 5 Hz (R_5_) and 20 Hz (R_20_) and reactance at 5 Hz (X_5_) [17]. Results were analyzed as absolute values and as percentages of predicted values (%) according to reference equations provided by the manufacturer [18].

Lung volume studies were carried out using a body-plethysmograph (Ganzhorn, Germany) according to ATS/ERS recommendations [19]. The following parameters were analyzed: airway resistance (RAW), expiratory airway resistance (RAWex), total lung capacity (TLC), residual volume (RV) and the RV/TLC ratio and expressed as percentages of predicted values according to ATS/ERS recommendations [19, 20].

Single-breath diffusing capacity of the lung for carbon monoxide (DL_CO_) was measured using a rapid carbon monoxide and helium analyzer (Ganzhorn, Germany), which was calibrated prior to each measurement. Values for DL_CO_ and DL_CO_ corrected for alveolar volume (V_A_) [DL_CO_/V_A_] were obtained and are reported as percent predicted values [21].

### Exhaled breath temperature

EBT was measured using X-Halo® device (Delmedica Investments, Singapore) according to previously validated method [22]. Patients were requested to inhale freely through the nose and to exhale through the mouth into the device at a rate and depth typical of their normal tidal breathing pattern. The maneuver was continued until the software of the instrument indicated that the measured value was stable, thus fulfilling the criteria of a previously described mathematical model. The tests were carried out at room temperature of 19–25 °C, and at relative humidity of 30–60% in the lung function lab where the atmosphere is controlled and measured. EBT was measured twice on the same occasion (during the initial visit); (1) baseline measurement before any other procedure (lung function, bronchodilator test, 6MWT) at least 1 h after the last smoked cigarette (EBTb) and (2) done only in active smokers 15 min after a smoked cigarette (EBTc) and recorded with precision of 1/100 of a °C. No other procedure apart from cigarette smoking was carried out between the two EBT measurements.

### Blood sampling and storage

Before initializing the sample collection process, it was important to ensure the correct order of blood collection. The PAXgene blood RNA tube had to be the last tube drawn in the study procedure process. Before sample collection, all tubes were labeled with patient identification number. Blood samples for serum were drawn at minimal volume of 3 ml in serum separation vacuum tubes (containing Z Serum Clot Activator gel) and sent to the laboratory. Samples were kept at room temperature for at least 30 min, but had to be processed within 2 h of blood collection. Upon centrifugation at 3000 rpm for 10 min, a minimum of 300 μl of serum was separated for further detection of hs-CRP level. The rest of the serum sample from every subject was transferred to a cryotube vial and stored at −20 °C.

Blood samples for plasma were drawn at minimal volume of 3 ml in K2EDTA vacuum blood collection tubes and were inverted several times to ensure proper mixing of additive with blood. Samples were sent to the laboratory where 200 μl of blood was separated for the purpose of complete blood cell hematological analysis. The remaining blood volume was kept at room temperature for at least 30 min, but had to be processed within 2 h of blood collection. Samples were then centrifuged at 3500 rpm for 10 min. The plasma sample from every subject was transferred to a cryotube vial and stored at −20 °C.

Blood samples for DNA extraction were drawn at minimal volume of 2 ml in K2EDTA vacuum blood collection tubes and were inverted several times to ensure proper mixing of the additive with blood. Samples were sent to the laboratory where they were kept at room temperature for 30 min, and inverted again before their transfer to a cryotube vial which was stored at −20 °C.

Blood samples for RNA extraction were drawn at volume of 2.5 ml in PAXgene blood RNA tubes, which were kept at room temperature prior to use. After blood collection, the PAXgene blood RNA tubes were immediately gently inverted 8–10 times to ensure proper mixing of additive with blood, after which they were stored at −20 °C.

Laboratory analyses were done in local laboratories and included complete blood count, white blood cells differential count, hematocrit, hemoglobin and hs-CRP.

Functional exercise capacity was assessed using 6MWT according to the ATS guidelines and expressed as walked distance in meters and as % of predicted according to Trooster et al. [23, 24].

### Data analyses

Data analyses are envisaged using STATISTICA version 12 (StatSoft, Inc., OK, USA), MedCalc Statistical Software version 16.8.4 (MedCalc Software bvba, Ostend, Belgium; https://www.medcalc.org; 2015) and RUMM2030 (RUMM Laboratory, Perth, Australia). Sample size calculation was done based on the following assumptions: we expected to find 25% patients in different stages of COPD according to the airflow limitation. We therefore expected that the sample would consist of 75% of ‘healthy’ and symptomatic smokers, 12.5% patients with COPD GOLD 1, 6.25% in GOLD 2 and 6.25% in GOLD 3 or 4 stages at initial visit with the expected difference in the MARKO questionnaire scores of 2 points and SD od 2.5 points between ‘healthy’ smokers vs. symptomatic smokers vs. COPD GOLD 1/2 having a statistical power of >80% with alpha = 0.05 for the sample size of at least 500 subjects. The expected yearly incidence rate for GOLD 1 and progression from GOLD 1 to GOLD 2 is planned at 10/per 100 patient-years.

Phase I data analysis will primarily focus on primary validation of the MARKO questionnaire (its psychometric characteristics), convergent and discriminant validity comparing data between different subgroups and with other HRQoL questionnaires (CAT and SGRQ). Categorical data will be compared between subgroups using chi-square test or Fisher exact test and continuous variables using Mann-Whitney *U*-test and Kruskal-Wallis ANOVA (non-normal distribution expected). Metric characteristics of the MARKO questionnaire will also be analyzed using Cronbach’s alpha, Lin’s concordance and Spearman’s correlation coefficients, analyzing inner consistency, test-retest reliability, and association with other measures of HRQoL and health status.

Phase II data analysis will focus on secondary validation of the MARKO questionnaire to determine the construct validity and predictability (alone or in combination with other markers) for future development and/or progression of COPD. Construct validity of the MARKO questionnaire will be assessed using factorial analysis to confirm the number of factors the questionnaire is measuring with calculations of inter- and intracorrelations between the factors and items. Primary objective will be to create a questionnaire with the smallest number of items with reliable predictive properties. Identifying items for potential deletion will be based on a hierarchical process: age and sex bias, floor and ceiling effects, item to total correlation and tests of redundancy (inter-item correlation). Rasch analysis will be used to identify items with the best fit to a predictive model. Utility of different markers for disease progression will be assessed using generalized linear/nonlinear regression models and expressed as odds ratio (OR) with 95% confidence intervals (CIs). Predictive power for the models will be presented using receiver operator curve (ROC) analysis with AUC (with 95% CIs) together with associated criterion, sensitivity, specificity and positive (PPV) and negative predictive (NPV) values. *P* < 0.05 will be used as statistically significant for all analyses with correction for multiple comparisons.

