University Hospital Center Zagreb, Zagreb, Croatia	Assoc.[name] [name], MD, PhD	Subinvestigator
Special Hospital for Lung Diseases, Zagreb, Croatia	[name] [name]	Subinvestigator
	[name]	Subinvestigator
General practice offices, Osijek, Croatia	[name], PhD	
	[name]	
	[name]	
	[name]	
	[name]	
	[name]	
	[name]	
	[name]	
	[name]	
General Practice offices, Split, Croatia	[name]	
	[name]	
	[name]	
	[name]	
	[name] [name]	
	[name]	
General Practice offices, Zagreb, Croatia	[name]	
	[name]	
	[name]	
	[name]	
	[name]	
	[name]	
General Practice office, Donji Muć, Croatia	[name]	
General Practice office, Postira, Croatia	[name]	
General practice office, Rijeka, Croatia	Assoc.[name] [name], MD, PhD	
General Practice office, Strmec Samoborski, Croatia	[name]	

*Primary endpoint:* to develop and validate the MARKO questionnaire to be used alone or together with other markers to identify subjects that will develop COPD.

*Secondary endpoints:* (a) to evaluate psychometric characteristics of the MARKO questionnaire; (b) to evaluate if the developed screening questionnaire together with the COPD-6^TM^ measurement discriminates COPD patients with GOLD stage 0 (symptomatic smokers) and GOLD 1 from ‘healthy’ smokers and patients with COPD GOLD 2 or higher based on the evaluation made by the pulmonologist; (c) to determine the rate of progression of COPD in patients with GOLD 0 during the follow-up; (d) to determine the prevalence of concomitant disorders in this population; (e) to identify diagnostic parameters that are most sensitive for early impairment in COPD (best discriminate between COPD GOLD 0 and GOLD 1); (f) to compare the MARKO questionnaire with diagnostic tools used for evaluation of patients (SGRQ, CAT, history, physical, lung function, 6MWT); (g) to assess the prevalence of different stages of COPD (specifically GOLD 0 and GOLD 1) in the population at risk for COPD and in the general population.

MARKO is a two phase study: Phase I - a cross-sectional; Phase II - prospective, observational, non-interventional cohort study. Flow diagram of subjects through the MARKO study is presented in Fig. 1 and all the assessments during the study are summarized in Table 2.

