Phase I of the MARKO study will be used to test the psychometric characteristics of the MARKO questionnaire; to evaluate discriminative power of the MARKO questionnaire together with COPD-6™ measurements between different developmental stages of COPD; to identify diagnostic parameters that are most sensitive for early impairment in COPD (discriminate between COPD GOLD 0 and 1); to compare the MARKO questionnaire with other measures used to evaluate patients (HRQoL, history, physical, lung function, functional capacity); and to assess the prevalence of different stages of COPD (specifically GOLD 0 and 1) in the population at risk for COPD. Preliminary data from Phase I of initial validation of the MARKO questionnaire showed the potential for the MARKO questionnaire to assess early health status changes in smokers at risk for chronic obstructive pulmonary disease [31]. Although exclusion criteria were introduced to exclude subjects with acute/subacute clinical disorders or states of recovery from major clinical disorders representing an absolute or relative contraindication for spirometry or significantly influencing the diagnostic process, the data analysis showed that more than half (56.3%) of the recruited subjects had one or more (up to 3) comorbidities (28.6% hypertension, 10% dyslipidemia, 5.2% diabetes and 4.9% peptic syndrome, etc.) [31].

Phase II of the MARKO study will be used to test the primary endpoint of the study: to validate the MARKO questionnaire as a tool to be used alone or combined with other markers in identifying subjects at risk (smokers/ex-smokers with relevant exposure to tobacco smoke) who will develop COPD during the follow-up. Based on previously published data that EBT could be a sensitive marker of airways inflammation [21] we introduced it as a possible predictive marker for future COPD. Recently published data from Carpagnano GE et al., and from our group (preliminary data from the MARKO study) showed the sensitivity of EBT to cigarette smoke and the potential to predict future development of COPD in current smokers [32, 33]. All other parameters were measured/gathered at the start of the study for a detailed phenotype/endotype of recruited subjects and as possible predictive markers for future COPD.

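### Phase II chooses predictors and reports their accuracy in the same subjects on the same outcome, and calls this validation; for marker combinations, outcome-selected items and a data-chosen cut-off that accuracy is optimistic

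*Protocol article*

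**What the plan says.** The primary endpoint (Methods, aim, design and setting) is "to develop and validate the MARKO questionnaire to be used alone or together with other markers to identify subjects that will develop COPD". The Discussion assigns this to the second phase: "Phase II of the MARKO study will be used to test the primary endpoint of the study: to validate the MARKO questionnaire as a tool".

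The Phase II part of Data analyses contains, in order:
- the aim: "Primary objective will be to create a questionnaire with the smallest number of items with reliable predictive properties";
- the deletion rules: "Identifying items for potential deletion will be based on a hierarchical process: age and sex bias, floor and ceiling effects, item to total correlation", followed by inter-item redundancy;
- the Rasch step: "Rasch analysis will be used to identify items with the best fit to a predictive model";
- the marker models: "Utility of different markers for disease progression will be assessed using generalized linear/nonlinear regression models";
- the report: "Predictive power for the models will be presented using receiver operator curve (ROC) analysis with AUC", with confidence intervals, the associated criterion, sensitivity, specificity, PPV and NPV.

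The design section gives incident COPD at 2 and 5 years two uses: to find the parameters most sensitive for early impairment, and to determine how well the questionnaire predicts, alone or with other markers. All Phase II subjects come from Phase I. The one safeguard named is correction for multiple comparisons.

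**The concern.** When predictors, weights or a threshold are chosen because they fit a set of outcomes, accuracy measured on those outcomes includes the chance part of the fit. This is apparent performance, and it falls in new subjects. The article assigns choosing and measuring to the same people and outcomes and gives the result the name validation.

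The Background asks for a tool with high specificity, and the Discussion wants it highly specific so that earlier intervention does no harm. Inflated sensitivity and specificity would therefore bear directly on the intended use.

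The Rasch sentence has a separate fault. Rasch item fit measures agreement with a unidimensional measurement model and does not use later COPD. It cannot find the items that predict best, and an item that fits badly may still predict well.

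**Working it through.** **The plan's own calculation.** The document gives no expected AUC, sensitivity or specificity. Its only power figure is for a cross-sectional score difference of 2 points with SD 2.5 and alpha 0.05 (taken as two-sided). The number per group for 80% power is 2 × (1.960 + 0.842)² × (2.5/2)² = 24.5, so 25. With 500 subjects every pairwise power exceeds 99%, so the stated >80% holds as a lower bound. That calculation says nothing about prediction.

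**Events from the plan's figures.** Phase II takes up to 500 subjects without COPD or in GOLD 1. Using the expected mix (75% and 12.5% of the sample), the COPD-free number is 500 × 75/87.5 = 429. At 10 per 100 patient-years, with no dropout:
- 2 years: 429 × (1 − e^−0.2) = 78 new cases;
- 5 years: 429 × (1 − e^−0.5) = 169 new cases.

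**Where the outcome enters.**

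| Step | Uses incident COPD? | Optimism |
|---|---|---|
| Age/sex bias, floor/ceiling, item-total, inter-item | No | Little |
| Rasch item fit | No, despite the wording | Little |
| AUC of unchanged 0–57 total | Direction and weights fixed in advance | None |
| Items chosen or weighted for prediction | Yes, if done | Yes |
| Choice and fitting of marker combinations | Yes | Yes |
| Criterion taken from the same ROC curve | Yes, if so chosen | Yes |

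**Illustrative size.** The following are assumptions and are not in the documents: inter-item correlation 0.4; 40 candidates, made up of the 18 items plus 22 other non-omics markers that carry no information; a true total-score AUC of about 0.70; logistic models; and a cut-off at the maximum Youden index (sensitivity + specificity − 1). Each setting was simulated 150 times, and each model and cut-off was then applied to 5,000 new subjects.

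429 subjects, 78 events (2 years):

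| Procedure | AUC apparent | AUC new | Sens/spec apparent | Sens/spec new |
|---|---|---|---|---|
| Fixed 18-item total, cut-off from data | 0.705 | 0.706 | 0.69/0.65 | 0.65/0.64 |
| 40 candidates screened at p<0.05 | 0.75 | 0.66 | 0.71/0.70 | 0.56/0.67 |
| All 40 candidates fitted | 0.80 | 0.64 | 0.75/0.72 | 0.51/0.67 |

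For the fixed total only the cut-off is affected: the Youden index is 0.34 apparent and 0.29 in new subjects.

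If nothing predicts COPD, screening 40 candidates at p<0.05 gives an apparent AUC of 0.61 against a true 0.50.

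The gap depends on the number of events. Across the selected or fitted models with true signal:
- 169 events at 5 years: about 0.03 to 0.11 in AUC (screened model 0.741 against 0.668);
- 300 subjects at 2 years (30% loss assumed, 54 events): about 0.06 to 0.21.

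**The case against.** Four points can be made for the plan.

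- **Item deletion.** A reader might infer that items are deleted on the outcomes that later validate the form. The text does not support this: none of the listed criteria uses COPD, and Rasch fit does not either. This objection stands, and the point does not rest on item deletion. The outcome could enter item choice only through the stated aim of predictive properties.
- **The questionnaire itself.** A reader might also infer that even an uninformative questionnaire would show an AUC well above 0.5. That is not so for the form described in Methods. It is one summed score with a fixed direction, so its expected AUC without association is 0.50. This stands too. Inflation needs items, weights or markers selected on outcome.
- **The cut-off.** The article does not say how the associated criterion is chosen. The claim about it is therefore conditional on its coming from the same curve.
- **Missing detail.** An article may leave internal validation to the full protocol or analysis plan, neither of which is shown. The absence of a bootstrap or hold-out is accordingly no fault in itself. But the article does fix something: one cohort and one outcome serve both to choose parameters and to show predictability, and the result is called validation of the primary endpoint. The safeguard it names controls p-values and does not correct an AUC or a threshold. The Rasch sentence is wrong as worded, whatever another document adds.

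**Conclusion.** The point holds in a limited form. Followed as written, Phase II yields apparent accuracy, labelled validation, for marker combinations, for any items chosen or weighted on outcome, and for a cut-off if it is taken from the same ROC curve. The AUC of the unchanged total score is sound.

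Under the stated assumptions the excess at 2 years is about 0.09 in AUC and 0.15 in sensitivity for a screened 40-candidate model. It is smaller with the 5-year events and larger with fewer events. The number of candidates, how many of them carry signal, the inter-item correlation, the true AUC and the dropout are not in the documents, so these figures show scale and are not forecasts. Omics markers would add candidates beyond those counted here.

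This should be fixed before Phase II outcomes are analysed. It does not undermine the cohort or the data collection.

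**What to change.** 1. Carry out the outcome-free item reduction, including factor analysis and Rasch fit, on Phase I baseline data. Lock the short form and its scoring before Phase II outcomes are linked, then test that single score.
2. For marker combinations and the cut-off, repeat the whole selection procedure inside bootstrap or cross-validation. Report optimism-corrected AUC, sensitivity and specificity as the headline, with apparent values beside them if wanted. State how the criterion is chosen.
3. Call this internal validation and keep the unqualified word for independent subjects. Testing a model locked at 2 years on the 5-year outcomes of the same people would not be independent.
4. Reword the Rasch sentence: Rasch analysis selects items for fit to a measurement model, and prediction is judged by the outcome model.

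The cost is wording, some computing time and lower headline accuracy. No further subjects or visits are needed.
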